### ***1.2 Procedure***

In the Rotterdam Rijnmond area 30 YHC-teams will participate in the study. The YHC-teams will be selected from four practice organizations for preventive Youth Health Care for preschool children (Ouder- en Kindzorg organisaties; Consultatiebureaus). These organizations are Ouder- en Kindzorg Rotterdam (OEK) with circa 28 YHC-teams and 6.500 births per year; De Stromen Opmaat Groep in Dordrecht area with circa 14 YHC-teams and 3.400 births per year; Careyn in Schiedam/Vlaardingen area with circa 7 YHC-teams and 2.000 births per year; and Thuiszorg de Zellingen in Capelle a/d IJssel with circa 3 YHC-teams and 700 births per year.

The Youth health Care professionals will inform parents of 2-year olds about the study, prior to their regularly scheduled routine visit at age 24 months. The parents will be invited to provide written informed consent.

As stated above, for the purpose of Part 2 of the study (see below), at random 15 teams will be assigned to apply the BITSEA as screening tool using the so-called Youth Health Monitor (YHM) at age 24 months. Fifteen other YHC-teams (randomized) will not use BITSEA as screening tool, but the parents in the Control group will be invited to additionally complete the BITSEA, but its results will not be used by the YHC-professional (blinded).

According to regular practice parents that visit the YHC-center when the child is 24 months old, complete the Youth Health Monitor (a health questionnaire); for Turkish and Moroccan parents bilingual forms are available; if necessary parents get assistance at the YHC-center.

Separately from the Youth Health Monitor, at child age 24 months all participating parents will be invited to complete a concise additional questionnaire anonymously. In the Intervention group this questionnaire contains the CBCL 1,5-5. In the Control group this questionnaire contains the CBCL 1,5-5 and the BITSEA. As stated above, scores from this additional questionnaire at age 24 months will not be used in the routine health assessment (see schematic Overview of the study in Annex).

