### ***1.1 Design and study population (see annex with overview)***

#### **A. Community sample including parents that visit regular preventive YHC at age 2 years**

A large community sample of 2-year olds (and their parents) in the Rotterdam Rijnmond region with both metropolitan areas with extensive and varied non-Dutch communities and non-metropolitan areas representative of the Dutch population at large, will be used in Part 1 of the study. The study will be carried out by 30 YHC-teams from 4 organizations for preventive YHV in the region. They will obtain informed consent from parents with 2-year olds eligible for the routine health assessment by preventive YHC at age 24 months.

Net 3.000 parents/2-year olds will complete the BITSEA in the course of the study at age 24 months.

Please note that for the purpose of Part 2 of the study (see below) from the total of 30 participating YHC-teams in the study, at random 15 YHC-teams will be assigned to apply the BITSEA as a new screening tool at age 24 months (Intervention condition). The other 15 YHC-teams will apply 'usual care', i.e. application of the KIPPPI-'Consultatie Bureau Signalerings Instrument 2-jarige' (Control condition).

In the Control group in which the KIPPPI-2 is used as a screening tool, the parents will also complete the BITSEA (blinded for the YHC-professionals; in the Control group the YHC-professionals will not use the BITSEA results in the process of health assessment and early detection of emotional and behavioral problems).

In addition to and separately from the Youth Health Monitor, the 3.000 participating parents of 2-year olds in the study will be invited to complete the Child Behavior Checklist 1,5-5 (CBCL 1,5-5), a parent-completed 99-item questionnaire. The CBCL 1,5-5 will be applied to determine the concurrent validity of the BITSEA. The CBCL 1,5-5 is an internationally validated measure that allows making a (provisional) diagnosis respectively problem definition; the CBCL is widely used as gold standard in validation studies (Carter et al, 2004; Achenbach et al, 2000; Reijneveld et al, 2004; Zeijl et al, 2005).

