### ***2.2 Procedure***

Prior to the regularly scheduled, routine visit to the preventive YHC-center at child age 24 months, all parents of a 2-year old will be fully informed and invited to participate with their child in the study; written informed consent will be obtained.

As described in paragraph 1.2 (above) prior to the visit, the parents complete the Youth Health Monitor questionnaire as part of the normal routine at the YHC-centers. In the Control group, as usual, the Youth Health Monitor questionnaire includes the KIPPPI-2. In the Intervention group the Youth Health Monitor includes a new questionnaire, i.e. the BITSEA.

As stated above bilingual versions (Dutch; Turkish/Arabic) are available and help can be provided by the YHC-center as part of the regular procedures.

Separately from the Youth Health Monitor, at child age 24 months all participating parents will be invited to complete a concise additional questionnaire anonymously. In the Intervention group this questionnaire contains the CBCL 1,5-5. In the Control group this questionnaire contains the CBCL 1,5-5 and the BITSEA. As stated above, scores from this additional questionnaire at age 24 months will not be used in the routine health assessment (see schematic Overview of the study in Annex).

Trained YHC-professionals (see below for details regarding the training) use either the BITSEA or the KIPPPI-2 as screening tool during the visit. According to the existing protocols, professionals will make use of cut-off points based on the 90th percentile (p90) of age-appropriate normative samples for interpretation of test results, next to other professional

---

observations in the Intervention group (BITSEA; see Briggs-Gowan MJ et al. Brief Infant Toddler Social and Emotional Assessment - BITSEA Manual. New Haven: Yale University; 2005) as well as in the Control group (KIPPPPI-2; see the website of KIPPPPI-2 <http://www.kippipi.nl/>; Jeugdmonitor Rotterdam, 2004).

Twelve months after the 24 months YHC-visit, so at age 36 months, all participating parents in the study will be invited to complete a follow-up questionnaire including BITSEA, CBCL 1,5-5, and items on use of care, items on satisfaction with YHC, and if applicable referral and follow-up care, and satisfaction regarding referral and follow-up.

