#### **Outcomes**

- CBCL 1,5-5 at baseline and 12-month follow-up (CBCL 1,5-5 scores are considered the primary outcomes)
- BITSEA at baseline and 12-month follow-up
- YHC-professional problem diagnosis and treatment/referral decisions at baseline and during follow-up (Reijneveld et al, 2004; Zeijl et al, 2005)
- Entries in the regional Youth Care Registries (SISA/SJS) at baseline and during follow-up (SJS, 2006)
- Child health-related quality of life (General health perceptions subscale of the ITQOL; Raat et al, 2006)

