### **2.4 Data analysis**

Multilevel analyses will be applied to allow for dependency between the individual measurements within the randomized YHC-teams (Campbell et al, 2004; Twisk, 2006). Multilevel linear regression analyses will be conducted for the continuous outcome variables with group (intervention or control) as independent variable and baseline values and potential confounders as covariates. Multilevel logistic regression will be performed in case of dichotomous outcome variables. Interaction effects by gender and ethnic background will be explored by introducing an interaction term into the regression analyses (Twisk, 2006).

Adherence to and satisfaction with the distinct elements of the early detection procedure by parents and professionals will be described.

Costs and effects will be evaluated for the purpose of a cost-benefit analysis.

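### The 24-month research questionnaire is to be completed anonymously, which contradicts analyses that need it linked to the same child's other records

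*Protocol*

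**What the plan says.** Protocol 1.2 (Procedure) states that, apart from the Youth Health Monitor, at 24 months "all participating parents will be invited to complete a concise additional questionnaire anonymously". Section 2.2 repeats the instruction for Part 2: parents "complete a concise additional questionnaire anonymously".

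The content of the form differs by group: "In the Intervention group this questionnaire contains the CBCL 1,5-5", whereas "In the Control group this questionnaire contains the CBCL 1,5-5 and the BITSEA". In the Intervention group the BITSEA sits in the Youth Health Monitor, a different form.

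The same protocol plans these uses of the form:

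- **Section 2.3, Outcomes:** "CBCL 1,5-5 at baseline and 12-month follow-up (CBCL 1,5-5 scores are considered the primary outcomes".
- **Section 2.4:** multilevel linear regression "with group (intervention or control) as independent variable and baseline values and potential confounders as covariates".
- **Section 1.1 A:** "The CBCL 1,5-5 will be applied to determine the concurrent validity of the BITSEA".
- **Section 1.4:** discriminative validity sets the BITSEA against what the professional found, with referral as one of the criteria.
- **Section 2.5:** a detectable difference at follow-up is given for children with psychosocial problems at baseline, taken as 210 of the 2,100 with complete data.

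Sections 1.2 and 2.2 also say, as a separate statement, that scores from this form play no part in the routine assessment.

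**The concern.** An anonymous form carries nothing that ties it to a child. Several planned analyses pair a value on this form with a value recorded elsewhere for the same child: the Youth Health Monitor, the visit record, the registry or the 36-month questionnaire. If the instruction is carried out as written, those pairs cannot be formed.

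This is a data-collection matter that no analysis plan can repair. Forms gathered without an identifier over the 21-month inclusion period (Annex III) stay unlinked. If parents are told the form is anonymous and it is nevertheless coded, the study contradicts what it told them. Parts of Research questions 1 and 2 depend on the answer.

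**Working it through.** **1. The plan's own numbers.** 6,000 invited × 0.50 = 3,000 included, or 1,500 per group (Annex III). 3,000 × 0.70 = 2,100 with complete data (2.2). 2,100 × 0.10 = 210 with problems at baseline (2.5). All reproduce. The figure of 210 presupposes that baseline problem status is known for the children who are followed up.

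**2. Which analyses need a link to the anonymous form.**

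| Analysis | Where the two values sit | Under literal anonymity |
|---|---|---|
| 36-month CBCL adjusted for baseline CBCL (2.4) | Anonymous form; 36-month form | Cannot be fitted |
| BITSEA with CBCL, Intervention (1.1 A, 1.4) | Youth Health Monitor; anonymous form | Lost, about 1,500 children |
| BITSEA with CBCL, Control | Both on the anonymous form | Unaffected |
| BITSEA with professional findings or registry, Control (1.4) | Anonymous form; records | Lost |
| BITSEA with professional findings, Intervention | Youth Health Monitor; records | Unaffected |
| Baseline-problem subgroup at 36 months (2.5) | Depends on the definition, which 2.5 does not give | Lost if defined by the CBCL or by the Control-group BITSEA |
| Unadjusted 36-month comparison by group | 36-month form, not described as anonymous | Unaffected |
| Clinical sample (1.1 B) | Recruited through other agencies | Not covered by the instruction |

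**3. Precision lost with the baseline covariate.** Inputs: ICC 0.10 (2.5); 30 teams and 2,100 completers, so 2,100 / 30 = 70 per team. The correlation r between baseline and follow-up CBCL is not in the protocol; 0.5 to 0.7 is assumed.

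The variance of a team mean, in units of the total variance, is ICC + (1 − ICC)/m:

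- No adjustment: 0.10 + 0.90/70 = 0.1129.
- Child-level adjustment, r = 0.5: 0.10 + 0.90 × (1 − 0.25)/70 = 0.1096.
- Child-level adjustment, r = 0.7: 0.10 + 0.90 × (1 − 0.49)/70 = 0.1066.

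Ratios: 0.1129/0.1096 = 1.03 and 0.1129/0.1066 = 1.06. The variance of the group effect rises by about 3-6%. The detectable difference rises by the square root of this, about 1.5-3%.

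If baseline explained team differences in the same proportion as child differences, the ratio would be 1/(1 − r²), which is 1.33 at r = 0.5 and 1.96 at r = 0.7. The protocol gives no figure for how much of the team variation baseline explains.

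**The case against.** The strongest reply is that the word is a slip. Parents give written consent, the same parents are invited again at 36 months, and records and registry entries are retrieved per child. The 24-month measures are listed together as available subject to consent (1.3), and the Summary describes the CBCL as blinded for YHC. All this points to participants whom the study can identify, and to a form merely hidden from YHC staff. In addition, the overview figure in the Annex, to which both procedure sections refer, is not shown in the copy reviewed, and the consent pages were removed. A linkage step there cannot be ruled out.

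The likely intention is conceded. The contradiction remains, because the protocol already states concealment separately. Read plainly, the extra word adds something different, and it is the instruction from which forms and parent information would be prepared.

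A reader might infer more than the documents support:

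- **That the trial's main comparison fails.** It does not. The 36-month form is not called anonymous, so an unadjusted comparison by group remains. The 8.0-point detectable difference in 2.5 shows no baseline-correlation term.
- **That validity is lost throughout.** Control-group concurrent validity and Intervention-group comparison with professional findings need no link to this form.
- **That the subgroup analysis is impossible in any case.** Section 2.5 names no defining instrument. The professional's diagnosis or the screening tool in the Youth Health Monitor lies outside the anonymous form. With the screening tool, however, the groups would be classified by different instruments (BITSEA and KIPPPI-2).
- **That the variance of the effect grows 1.3 to 2.0 times.** That ratio describes child-level residual variance. It carries over to the group effect only if baseline explains team differences equally well, which the protocol does not say.

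**Conclusion.** The point holds as an internal contradiction that must be corrected before forms and parent information are issued. Taken literally, anonymous completion removes four things:

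- the baseline CBCL from the adjusted model;
- concurrent validity in the Intervention group (about 1,500 children);
- the link from the Control-group BITSEA to professional findings and registry entries;
- follow-up of any baseline-problem subgroup defined by this form.

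The cost in precision to the main comparison is modest: about 3-6% in variance, given ICC 0.10, 70 completers per team, an assumed r of 0.5-0.7 and adjustment acting only between children within teams. It is larger if baseline also explains team differences. The main damage is to the validation work and to analyses that need a child's own baseline. The conclusion rests on the visible text containing no study number or key.

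**What to change.** In sections 1.2 and 2.2, replace the word for anonymous completion with: under a study number (pseudonymised), returned to the research team, which holds the key, and not disclosed to the YHC-professional. Add one sentence stating that this number links the form to the Youth Health Monitor, the child's records, the registry and the 36-month questionnaire. Check that the parent information and consent text say the same. If the Annex overview or consent text already describes such a code, bring the two procedure sections into line with it.

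The cost is a change of wording in two paragraphs, a check of the consent text and a number printed on the form. Parents may answer slightly less candidly than under true anonymity. Direct return to the research team and concealment from YHC staff limit that.

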### Numbers in the study:

A total of 6.000 parents/toddlers will be invited by the 30 participating Youth Health Care teams in the study. Assuming (at least) informed consent by 50%, 3.000 parents/toddlers will be included. All participating YHC-teams and each participating YHC-professional in the study will receive handy, clear, written instructions (fact sheets/charts) about the role of each participant in the study. Instructions will be discussed during regular professional meetings (prior to the start of the inclusion, and also repeatedly during the study). Specific competences that are necessary will be trained (but this is especially relevant for Part 2 of the study; see paragraph 2.2).

---

Independent of this instruction/training with regard to the study, in a separate, independent proposal, we have presented a plan for activities to promote the readiness for doing research and to promote the willingness to participate in an optimal way in effectiveness studies by YHC-professionals that will cooperate in the study. For that separate purpose we applied for a so-called “Praktijkbonus” (additional financial support) that will be used to support these efforts of the four practice organizations that cooperate in the study (please refer to the Annex ‘Praktijkbonus’ attached to this proposal).

### ***1.3 Measures at age 24 months***

(community sample ~ n=3.000; and ‘clinical’ sample ~ n=100)

Note: These measures are only available providing informed consent by the parents

- BITSEA
- KIPPPI-2 (only in the Control group, and in the ‘clinical’ sample; not in the Intervention group)
- CBCL 1,5-5
- Parent report of use of (mental) health services and other professional support
- Diagnosis and decisions regarding follow-up care or referral by the YHC-professional at regular YHC-visit at age 24 months (Intervention group and Control group; if available in ‘clinical’ sample) (Reijneveld et al, 2004; Zeijl et al, 2005)
- Entries in the child’s medical record/Youth Care record (‘clinical’ sample only)
- Entries in the child’s regional Youth Care Registries (SISA/SJS) (SJS, 2006)
- Socio-demographic characteristics

### ***1.4 Data analysis***

Test properties of the BITSEA will be described, including internal consistency, inter-rater reliability, factorial validity, concurrent validity with the CBCL 1,5-5, and discriminative validity (BITSEA results compared to professional findings). Receiver Operating Characteristic (ROC) curves for all possible cut-off points will be made available by using results of the ‘clinical’ sample. See Mackenbach et al (2008), page 240-253 for description of the test properties and procedures to evaluate the BITSEA as screening tool.

Two criteria will be used in this analysis: (a) a ‘clinical score’ on the CBCL 1,5-5; and (b) referral to Youth Care/Child Mental Health Care (and additionally other professional diagnoses by YHC-professionals or Youth Care/Mental Health Care professionals).

Normative data and cut-offs will be produced based on the total community sample. All test results will be explored and described for subgroups of children from ethnic minorities.

---

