## Research questions:

### **PART 1 OF THE STUDY: ‘TEST PROPERTIES’**

1. What are the sensitivity, specificity, predictive value of test results, and other psychometric test properties (including reliability, factorial validity, concurrent and discriminative validity) of the BITSEA?

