## B. 'Clinical' sample

Additionally, a 'clinical' sample of net 100 toddlers that are circa 2 years old (18-30 months old) and that have been referred to Youth Care or Youth Mental Health Services will be drawn through Youth Care/Mental Care agencies in the Rotterdam Rijnmond area. Parents of these 2-year olds will also complete the BITSEA, the KIPPI-2, and the CBCL 1,5-5. Given informed consent by the parents, the diagnosis regarding the child will be retrieved from the (medical) chart. Data from the 'clinical' sample will be used to add to the validation of the screening tools.

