### ***1.5 Power considerations***

Since in Part 1 of the study no hypotheses are tested, power calculations are not really applicable. Nevertheless remarks can be made on the precision of the estimates this part of the study will yield.

A sample of 3.100 toddlers (3.000 of the community sample and 100 of the clinical sample) will allow to estimate the area under the Receiver Operating Characteristic (ROC) curve of about 0.90 with a 95% confidence interval of  $\pm 0.02$  (Hanley et al, 1982). A sub-sample size of 217 toddlers (e.g. a specific ethnic sub-group of 7% of the whole population, assuming equal prevalence of emotional and behavioral problems) will allow to estimate the area under the ROC curve of about 0.90 with a 95% confidence interval of  $\pm 0.08$ .

For evaluating concurrent validity of the BITSEA, correlations between specific BITSEA scores and specific, hypothesized CBCL 1,5-5 scores will be computed. Even in a sub-sample of 500 toddlers we can estimate a correlation of 0.20 (or higher) with a power of 99% ( $\alpha = 0.05$ ; one sided testing). An even smaller sub-sample of 50 toddlers (of a small specific ethnic sub-group for instance) will allow to estimate a correlation of 0.40 with a power of 90% ( $\alpha=0.05$ ; one sided testing).

Based on the entire community sample ( $n=3.000$ ) the p90 of the BITSEA Problem Total Score of 2-year olds can be estimated with a precision of  $\pm 3\%$  for boys and girls separately.

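### Sections 1.4 and 1.5 bring already-referred children into the ROC analysis, which would tend to overstate accuracy for routine screening; the ±0.08 subgroup precision also appears to rest on counting them as cases

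*Protocol*

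**What the plan says.** Research question 1 asks "What are the sensitivity, specificity, predictive value of test results" and other test properties of the BITSEA. The setting is preventive Youth Health Care; the Study Design section says the study is to inform a decision on screening by evaluating test properties in everyday practice there.

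Section 1.1 B adds a clinical sample of "net 100 toddlers that are circa 2 years old (18-30 months old"), all of them already referred to youth care or mental health services. Its stated role is to supplement the validation.

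Section 1.4 says that ROC "curves for all possible cut-off points will be made available by using results of the" clinical sample. It names two reference criteria: (a) a CBCL 1,5-5 score in the clinical range, and (b) referral, with other professional diagnoses in addition. It takes norms and cut-offs from the whole community sample.

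Section 1.5 gives its AUC precision for the two samples together: "A sample of 3.100 toddlers (3.000 of the community sample and 100 of the clinical sample"). At an anticipated AUC of 0.90, the 95% half-width is put at ±0.02. For 217 toddlers, "assuming equal prevalence of emotional and behavioral problems", it gives ±0.08. It does not state the number of cases behind either figure.

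**The concern.** Accuracy measured on children who have already been identified does not carry over to an unselected population. Every child in the clinical sample satisfies criterion (b) because that is how the child entered the study. Setting these children as cases against community children is a case-control contrast. It leaves out the milder and not yet recognised cases that a screening tool has to find, and it fixes the case share by design.

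The protocol does not say that the referred children are more severe. That is an inference, but a likely one. If it holds, sensitivity and AUC would look better than they are at the 24-month visit, and these results are meant to support a decision on wider use. The precision statement has the same root: it covers the pooled 3,100, so a reader cannot tell how far ±0.02 and ±0.08 depend on the enrichment.

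**Working it through.** **Inputs**
- AUC A = 0.90 and a two-sided 95% interval (z = 1.96): section 1.5.
- 3,000 community children, 100 referred children, subgroup of 217 (7% of 3,100): section 1.5.
- Hanley-McNeil standard error, the method of the paper that section 1.5 cites.
- Community prevalence 10%: an assumption. The figure appears only in section 2.5, for Part 2. Results at 7% and 5% are shown as a range.

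**Formula.** With n1 cases and n0 non-cases, a = A/(2 − A) and b = 2A²/(1 + A):

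SE² = [A(1 − A) + (n1 − 1)(a − A²) + (n0 − 1)(b − A²)] / (n1·n0), half-width = 1.96·SE.

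At A = 0.90, a − A² = 0.8182 − 0.81 = 0.00818 and b − A² = 0.8526 − 0.81 = 0.04263.

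**Step 1: reproduce the stated figures.** Take 10% of the community plus all 100 referred as cases: 300 + 100 = 400 against 2,700.
- SE² = (0.09 + 399 × 0.00818 + 2,699 × 0.04263)/1,080,000 = 0.0001097; SE = 0.0105; half-width 0.0205, stated as ±0.02.
- The same case share in 217: 217 × 400/3,100 = 28 against 189. SE = 0.0397; half-width 0.078, stated as ±0.08.

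**Step 2: take the referred children out as cases, at 10% prevalence.**
- Community only, 300 against 2,700: SE = 0.0120; half-width 0.024, which still rounds to ±0.02.
- Subgroup, 22 against 195: SE = 0.0446; half-width 0.087, which rounds to ±0.09. A result that rounds to ±0.08 needs 24 to 30 cases in 217 (11% to 14%).

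**Step 3: vary the assumed prevalence** (case numbers not rounded).

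| Community prevalence | 3,000, community only | With 100 referred as cases | 217, community share | 217, pooled share |
|---|---|---|---|---|
| 10% | 0.024 | 0.021 | 0.088 | 0.078 |
| 7% | 0.028 | 0.023 | 0.105 | 0.088 |
| 5% | 0.033 | 0.026 | 0.124 | 0.098 |

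**Step 4: the referred children as the only cases.** 100 against 3,000: SE = 0.0207; half-width 0.041.

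**Step 5: size of the bias.** The protocol gives no figure for it. With 400 pooled cases and common non-cases, the pooled AUC is a weighted mean in which referred cases carry 100/400 = 25%. It therefore exceeds the community AUC by a quarter of the gap between the two. With purely illustrative AUCs of 0.85 (community cases) and 0.95 (referred cases), the pooled value is (300 × 0.85 + 100 × 0.95)/400 = 0.875. If referred children were the only cases, the whole gap would enter.

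**Step 6: predictive value, if it were taken at the pooled case share.** Assume sensitivity 0.80 and specificity 0.90; neither is in the protocol. PPV = 0.8p/(0.8p + 0.1(1 − p)).
- p = 0.10: 0.47. At the pooled share 400/3,100 = 12.9%: 0.54.
- p = 0.05: 0.30. At the pooled share 250/3,100 = 8.1%: 0.41.

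**The case against.** The strongest reply is that the protocol does not commit to a pure contrast of referred against community children. Criterion (a) can yield cases in the community, because all community parents are invited to complete the CBCL. Criterion (b) can too, because professionals record problems and referral decisions at the visit. Cut-offs already come from the community sample, the clinical sample is only a supplement, and the allocation of samples to curves could be settled in an analysis plan that is not shown.

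Much of this stands, and it rules out three stronger readings that a reader might infer:
- *That ±0.02 is obtainable only by pooling all referred children as cases.* At 10% prevalence the community alone gives 0.024. Counting 0, 25, 50, 75 or all 100 referred children as cases among the 3,100 gives 0.0236 down to 0.0205. All of these round to ±0.02.
- *That the predictive values will be wrong.* The protocol lists them as a target but names no sample for them. The distortion in Step 6 is a risk left open, not a stated analysis.
- *That the stated precision is twice as good as the study can deliver.* The ±0.04 applies only if the 100 referred children are the sole cases, and section 1.4 does not say so.

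The reply does not remove the core. Section 1.4 does name the source of the ROC curves, and that source is not the population to be screened. Section 1.5 does quote precision for the pooled total without a case count. These are statements in the text, not details left for later.

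**Conclusion.** The point holds in a limited form. The protocol ties its ROC curves to children selected on one of its own reference criteria, while the question concerns unselected children at a routine visit. Followed as written, with these children counted as cases, the analysis would tend to overstate sensitivity and AUC. The direction rests on the likely but unstated premise that referred children are more severe; the size cannot be derived from the protocol.

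On precision, the two stated figures are together best matched by counting all 100 referred children as cases. Without them the main figure hardly moves at 10% prevalence (0.024 against 0.021), while the subgroup figure goes from ±0.08 to about ±0.09. Both results depend on the 10% borrowed from Part 2. At 5% they are ±0.033 and ±0.12, and even full pooling (0.026) would no longer round to ±0.02.

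**What to change.** In section 1.4, estimate the primary ROC curves, sensitivity, specificity and predictive values in the community sample, with the CBCL clinical score as criterion. Report the referred sample separately as known-groups evidence, and do not use it for predictive values.

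In section 1.5, state the assumed number of cases and restate the half-widths at AUC 0.90:
- community sample: about ±0.024 at 10% prevalence (±0.028 at 7%, ±0.033 at 5%);
- subgroup of 217: about ±0.09 at 10% (±0.12 at 5%);
- any curve with the 100 referred children as the only cases against 3,000: about ±0.04.

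The cost is a change of wording and a few numbers. The data are already due to be collected, and the only downside is slightly less favourable stated precision.

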Furthermore, during the regular visit at the YHC center at age 2 years, the YHC-professional will register (routinely) whether emotional or behavioral problems are present, and whether follow-up care or referral is recommended, according to professional judgment based on the protocols (in the Intervention group the BITSEA will be used; in the Control group the KIPPPI-2). Bilingual versions (Dutch; Turkish/Arabic) of the questionnaires will be offered.

---

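### In the Intervention group, section 1.4 compares the BITSEA with YHC-professional findings and post-visit referrals that the BITSEA itself helped to produce, so that part of the validation is partly circular

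*Protocol*

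**What the plan says.** All references are to the protocol.

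- Section 1.4 (Data analysis) lists among the test properties "discriminative validity (BITSEA results compared to professional findings". It names two criteria. Criterion (a) is a CBCL 1,5-5 result in the clinical range. The second criterion is given as "b) referral to Youth Care/Child Mental Health Care (and additionally other professional diagnoses by YHC-professionals or Youth Care/Mental Health Care professionals". Neither use of professional judgment is limited to one arm.
- Section 1.3 lists the judgment as a Part 1 measure in both arms: "Diagnosis and decisions regarding follow-up care or referral by the YHC-professional at regular YHC-visit at age 24 months (Intervention group and Control group".
- Section 1.1 A says how the judgment is reached: "according to professional judgment based on the protocols (in the Intervention group the BITSEA will be used; in the Control group the KIPPPI-2".
- Section 2.2 adds that "professionals will make use of cut-off points based on the 90th percentile (p90) of age-appropriate normative samples for interpretation of test results". The professional's own observations count as well.
- In the Control group parents also complete the BITSEA, but it is kept from the professional: "in the Control group the YHC-professionals will not use the BITSEA results in the process of health assessment".
- The 24-month CBCL is collected in a separate questionnaire that is not used at the visit in either arm (sections 1.2 and 2.2).

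**The concern.** A validity study needs a reference standard reached without knowledge of the test under study. In the Intervention group the test is an input to the reference. A child above the BITSEA cut-off is more likely to be recorded as having a problem, or to be referred, because of that score. Agreement then partly measures how far professionals follow the instrument, not whether the instrument finds problem children (incorporation bias). A larger sample does not remove it.

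At stake are the sensitivity, specificity, predictive value and AUC reported against one of only two named criteria for research question 1. The Relevance section says the study's results will inform decisions on nationwide implementation. The protocol protects the Control group and the CBCL from this problem; the comparison with professional judgment in the Intervention group is left unprotected.

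**Working it through.** **1. Which comparisons are touched**

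| Comparison | Did the BITSEA feed the reference? |
|---|---|
| CBCL criterion (a), both arms | No; kept out of the visit |
| YHC findings and post-visit referral, Control | No; BITSEA blinded, KIPPPI-2 used |
| YHC findings and post-visit referral, Intervention | Yes, in part |
| Clinical sample (section 1.1 B) | No; already referred |
| Normative data and p90 cut-offs | No; based on the community score distribution |

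The Intervention group is planned as 1,500 of the 3,000 community children (inclusion schedule).

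**2. Reproducing the plan's precision**

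Section 1.5 gives ±0.02 for an AUC of about 0.90 with 3,100 children. The Hanley-McNeil formula, for AUC A with n1 cases and n0 non-cases, is

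SE² = [A(1−A) + (n1−1)(P1−A²) + (n0−1)(P2−A²)] / (n1·n0), with P1 = A/(2−A) and P2 = 2A²/(1+A).

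At A = 0.90: P1 = 0.8182, P2 = 0.8526, A² = 0.81. Section 1.5 gives no case count. I assume 10% prevalence (stated in section 2.5 for Part 2) plus the clinical sample: 0.10 × 3,000 + 100 = 400 cases and 2,700 non-cases.

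SE² = (0.09 + 3.26 + 115.06)/1,080,000 = 0.0001096; SE = 0.01047; half-width = 1.96 × 0.01047 = 0.0205.

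The stated ±0.02 therefore reproduces with both arms counted. The subgroup figure does too: 217 children with 28 cases (7% of 400) give 0.078, against the stated ±0.08.

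**3. Precision for the professional-judgment criterion, same formula, AUC 0.90**

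- Both arms, 300/2,700: SE = 0.0120, half-width 0.024.
- Control only, 150/1,350: SE² = (0.09 + 1.22 + 57.51)/202,500 = 0.0002905; SE = 0.0170, half-width 0.033.
- Control with the clinical sample added, 250/1,350: half-width 0.026.

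**4. Direction and possible size of the bias**

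Nothing in the protocol says how strongly a positive screen moves the judgment, so every input here is an assumption.

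*Cut-off model.* BITSEA and KIPPPI-2 each have reliability 0.7. The professional's own impression shares 30% of its variance with severity and flags 10% of children. Both screens are cut at p90, and a given share of screen-positives is acted on, equally in both arms. Without any use of a screen, the AUC of the BITSEA against the judgment is 0.75. With half of the positives acted on, it is 0.825 in Intervention and 0.785 in Control. With equal arms and equal flagged shares, the pooled AUC is the mean, (0.825 + 0.785)/2 = 0.805, an excess over Control of 0.020. If 25% are acted on the excess is 0.011; if 75%, 0.028.

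*Weighted-score model.* BITSEA, KIPPPI-2 and other observation each correlate 0.6 with the true level, and the judgment is a weighted mean of screen and observation, cut at p90.

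| Weight on the screen | AUC Intervention | AUC Control | Pooled excess = half the difference |
|---|---|---|---|
| 0.25 | 0.821 | 0.726 | 0.05 |
| 0.50 | 0.930 | 0.739 | 0.10 |
| 0.75 | 0.987 | 0.726 | 0.13 |

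Sensitivity at p90 is 0.39, 0.59 and 0.81 in Intervention, against 0.28, 0.29 and 0.28 in Control.

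Both models agree on direction and disagree on size. The cut-off model is closer to the use of cut-offs described in section 2.2.

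**The case against.** The strongest case is that the point is narrow.

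- Section 1.4 does not say that criterion (b) is applied to the pooled community sample. It ties that sample to norms and cut-offs, and the ROC curves to the clinical sample. Part 1 tests no hypothesis, and an arm restriction could sit in an analysis plan that is not shown. This stands against any claim that the plan expressly pools. It does not remove the problem: section 1.3 lists the judgment in both arms as a Part 1 measure, and section 1.4 makes it a criterion without limit.
- Professionals use other observations too, and YHC diagnoses enter criterion (b) only as an addition to referral. This stands. The circularity is partial, and referral is touched only where it follows the 24-month visit.
- The Part 2 primary outcome (CBCL) and the randomised comparison are untouched. This stands, and it limits the severity.

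Three stronger readings are tempting, and the documents do not support them.

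- A reader might infer that BITSEA validity as a whole is circular. The table in the working shows otherwise.
- A reader might infer that wrong cut-offs would follow. Cut-offs come from percentiles of the community score distribution, which need no reference standard.
- A reader might infer that the bias is shown to exceed the claimed ±0.02. That precision is stated for an AUC near 0.90. At 0.75 the half-width is 0.029 (400/2,700) to 0.033 (300/2,700), and the cut-off model's excess of 0.011 to 0.028 lies below it. The weighted-score model would exceed it, but only through weights that the documents do not give.

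**Conclusion.** The point holds for discriminative validity against professional findings, and for the part of criterion (b) that rests on YHC diagnoses and on referrals following the 24-month visit, in the Intervention group only. Estimates there, and any pooled estimate, would be biased upward relative to the blinded Control group.

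The direction follows from the protocol's own procedures. The size cannot be derived from them: about 0.01 to 0.03 in pooled AUC under the cut-off model, and more if the judgment follows the score closely. Upward here means relative to the Control estimate, which itself measures agreement with an imperfect, KIPPPI-2-informed judgment and not accuracy against the true state.

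Severity: should be fixed. It concerns one of two validity criteria, and the data needed for an unaffected analysis are already planned.

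**What to change.** In section 1.4:

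- base the comparison with YHC-professional findings and post-visit referral on the Control group, where the BITSEA is blinded;
- report the same comparison in the Intervention group separately, labelled as BITSEA-informed;
- report the clinical sample's referral and chart diagnoses separately;
- keep the CBCL criterion in both groups.

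The cost is a few sentences and some precision. No new data are needed, since arm is known for every child. At an AUC of 0.90 and 10% prevalence the half-width goes from about 0.024 (300/2,700) to 0.033 (150/1,350). Section 1.5 should say that its ±0.02 does not apply to this criterion. Results for ethnic subgroups on this criterion will be correspondingly less precise.
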